## Background

### Child behavioural outcomes post-TBI

Paediatric traumatic brain injury (TBI) is a leading cause of disease burden in young children [1] and is associated with a range of poor psychological outcomes [2]. This includes post-injury behaviour changes [3], which can include excessive externalising behaviour, where the child demonstrates aggression, non-compliance, and irritability [4, 5]. The child may also exhibit poor self-regulation [6] and behave inappropriately in social settings [7, 8]. Internalising behaviours may also be present, in which the child is withdrawn and anxious [3], and parents may report personality changes [9].

The prevalence of such changes have been documented in 36% of severe TBI cases and 22% of moderate TBI cases [10]. Research also suggests that young children who experience a mild TBI requiring inpatient care are more likely to have behaviour problems than their uninjured peers [11]. Indeed, Catroppa and colleagues [12] showed that behaviour problems can emerge regardless of injury severity. These changes have been demonstrated to emerge early post-injury and increase over time [10] and may persist in the long-term [10, 11]. Behaviour disturbances post-injury have the potential to set individuals on a poor long-term trajectory, which may include difficulties in the classroom [10], anti-social behaviour [4], and increased risk of criminality [13]. Thus, problematic behaviour post-TBI is an outcome which requires attention and cannot be assumed to resolve without intervention.

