**Fig. 1 Fig1:**
[figure not shown]
Participant flow diagram

Data will be collected at four time points: (i) pre-injury functioning at the time of enrolment in the study and then (ii) pre-intervention, (iii) immediately post-intervention, and (iv) at the 4-month follow-up post-intervention. Data collected from those who complete the intervention will be compared with data collected at equivalent time points from a wait-list control group. This study has been granted ethics approval by the Human Research Ethics Committee of the Royal Children’s Hospital, Melbourne.

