#### Data collection

Data will be recorded to capture the number of eligible parents approached, the number who consented to the programme, and the number who successfully completed the programme, as well as reasons for non-participation and non-completion.

Questionnaires will be administered using a secure online data collection instrument (RedCap), with parents sent web links at the appropriate time points. Upon enrolment in the study, parents will be sent the web-link questionnaires and asked to complete the outcome measure questionnaires retrospectively, reporting on their child and family’s functioning prior to the TBI. It is acknowledged that this may be vulnerable to parent reporting bias, particularly where children are several years post-injury. However, evidence suggests that post-TBI behavioural problems may not emerge or present for intervention until several years post-injury [10, 11], which means that including families several years post-injury more closely mirrors the clinical setting. It therefore seems reasonable to include such families in this feasibility study. Future research may aim to minimise this bias by reducing the eligible time since injury.

Prior to commencing the programme, approximately 1 month following initial questionnaire completion, parents will be asked to complete the measures again with regard to their family and child’s *current* functioning. Outcome questionnaires will again be sent in the form of web links via email immediately after the intervention and 4 months post-intervention. The approximate timeline for completion of these questionnaires is summarised in Table 2.

**Table 2 Tab2:** Summary of measures used

Construct	Measure	Time point			
		1	2	3	4
Socioeconomic status	Social Risk Index	●			
Outcome measures					
Child behavioural outcomes	Child Behavior Checklist	●	●	●	●
Family outcomes	McMaster Family Assessment Device	●	●	●	●
Parental functioning					
Parental psychological distress	Depression Anxiety Stress Scales	●	●	●	●
Confidence and satisfaction in the parenting role	Parenting Sense of Competence Scale	●	●	●	●
Disciplinary practices	Parenting Scale	●	●	●	●
Programme satisfaction	Consumer Satisfaction Scale			●^a^	

Time point 1 = retrospectively completed about pre-injury behaviour, 2 = pre-intervention, 3 = post-intervention, 4 = 4 months post-intervention

^a^Intervention group only

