### Data analysis

Frequencies and percentages will be used to describe the population across key demographic and injury variables. We will compare the intervention and wait-list control groups across key variables (age at injury, injury severity, social risk, pre-injury behaviour, and pre-intervention behaviour) to detect any significant difference which may later compromise the generalisation of the findings.

Investigating the feasibility, clinical practicality, and acceptability of Signposts with videoconferencing support will be exploratory in nature. The objective is to collect information on ease of use, participant satisfaction, homework completion rates, programme completion and adherence, and attrition rates. Rates of programme attrition will be reported, as well as consumer satisfaction with the programme (reported as mean scores and percentages for items on the CSS).

To examine preliminary data on the impact of the programme on key outcome areas, we will compare the post-intervention scores on the CBCL scales, FAD, DASS, PS, and PSOC across the intervention and control groups and will report the mean and standard deviation of each group across these measures. To report preliminary findings on the maintenance of any treatment effects, means and standard deviations will be reported to assess any change within the intervention group from post-intervention to 4-month follow-up across the CBCL scales, FAD, DASS, PS, and PSOC. These findings may inform efficacy estimates for a larger RCT.

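### Maintenance at 4 months is assessed only by change within the intervention group, so natural course cannot be separated from loss or persistence of effect, although wait-list data are scheduled then

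*Protocol article*

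**What the plan says.** The Data analysis section of the protocol article names two analyses of the clinical outcomes.

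- **Between groups, at the end of the programme:** "we will compare the post-intervention scores on the CBCL scales, FAD, DASS, PS, and PSOC across the intervention and control groups", with each group's mean and SD.
- **Maintenance, at 4 months:** the stated purpose is "To report preliminary findings on the maintenance of any treatment effects", and the method is that "means and standard deviations will be reported to assess any change within the intervention group from post-intervention to 4-month follow-up", for the same set of measures.

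Three other places bear on this.

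- **Overall study design** lists the 4-month follow-up as the fourth time point and then says: "Data collected from those who complete the intervention will be compared with data collected at equivalent time points from a wait-list control group".
- **Table 2 (Data collection)** ticks the CBCL, FAD, DASS, PSOC and PS at all four time points, defined as "Time point 1 = retrospectively completed about pre-injury behaviour, 2 = pre-intervention, 3 = post-intervention, 4 = 4 months post-intervention". Its only group restriction, a footnote, is attached to the satisfaction scale.
- **Background, Child behavioural outcomes post-TBI**, says of behaviour changes after injury: "These changes have been demonstrated to emerge early post-injury and increase over time".

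**The concern.** A treatment effect is a contrast with what would have happened without the programme. It is maintained if that contrast persists, whether or not the treated arm's mean stays flat. The maintenance analysis uses the treated arm alone, so its result mixes the effect with whatever would have happened anyway between the end of the programme and 4 months.

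The Background gives a reason not to assume a flat course for child behaviour. If both arms worsened alike, the treated arm would appear to lose benefit although the contrast was intact. If untreated children improved while the treated arm stayed level, the arm would appear to hold its benefit although the contrast was shrinking.

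The Data analysis section adds that the findings may feed into efficacy estimates for a larger RCT. A statement about durability could therefore be carried into that trial's planning. The wording is also narrower than the comparison promised under Overall study design.

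**Working it through.** The protocol gives no figure for maintenance (no expected change, margin or interval), so there is nothing to reproduce. The check covers what the analysis estimates and then precision.

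**1. What within-arm change estimates.** On the CBCL T score lower is better. Let *d* be the natural change from time point 3 to 4, shared by both arms, and *L* the part of the effect lost over that time.

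- Change in the intervention arm = *d* + *L*
- Change in an untreated wait-list arm = *d*
- Difference in change = (*d* + *L*) − *d* = *L*

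Read as a measure of *L*, the within-arm change is wrong by *d*, which is the wait-list arm's own change.

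**2. Illustration.** The documents give no value for *d* or *L*; these values are assumed.

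| *d* | *L* | Within-arm change | Difference in change |
|---|---|---|---|
| +5 | 0 | +5 (looks like loss) | 0 |
| +3 | 0 | +3 (looks like loss) | 0 |
| 0 | 5 | +5 | 5 |
| −3 | 3 | 0 (looks maintained) | 3 |
| −5 | 5 | 0 (looks maintained) | 5 |

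The first and third rows give the same within-arm result from opposite situations.

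**3. Precision.** Inputs: SD = 10 (the T-score norm in Measures, Child behavioural outcomes); n = 15 per arm (Sample size); correlation *r* between time points 3 and 4, not given, assumed 0.5 to 0.8.

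- SD of change = 10 × √(2(1 − *r*))
- SE within arm = SD of change / √15; 95% half-width uses t(14) = 2.145
- SE of difference in change = SD of change × √(2/15); 95% half-width uses t(28) = 2.048

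| *r* | SD of change | SE within | Half-width | SE difference in change | Half-width |
|---|---|---|---|---|---|
| 0.5 | 10.0 | 2.58 | 5.54 | 3.65 | 7.48 |
| 0.7 | 7.75 | 2.00 | 4.29 | 2.83 | 5.79 |
| 0.8 | 6.32 | 1.63 | 3.50 | 2.31 | 4.73 |

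The ratio of the two SEs is √2 in each row (2.83 / 2.00 ≈ 1.41).

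For the between-group difference at time point 4, the unadjusted SE is 10 × √(2/15) = 3.65. Adjusting for the time-point-2 score multiplies this by about √(1 − *ρ*²), where *ρ* is the correlation between time points 2 and 4. At an assumed *ρ* = 0.7 that is 3.65 × √0.51 ≈ 2.61.

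**The case against.** The strongest counter-argument is that the sentence promises little: means and SDs, labelled preliminary, with no test, maintenance criterion or decision rule. Maintenance is one item within the last of four objectives in a study whose primary aim is feasibility and acceptability. The controlled comparison at the end of the programme is kept. All of this stands and limits the weight of the point. A reader might infer that natural course *will be mistaken* for maintenance or loss. The documents support only that the two *cannot be separated* by the analysis as worded.

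Second, the wait-list is an untreated comparator at time point 4 only if its families have not yet started the programme. The text does not say when they do, and the flow diagram (Fig. 1) is not shown. If some have started by then, the within-arm summary may have been chosen on purpose. This stands as an open question for the protocol to answer. It does not explain why Overall study design promises comparison at matching time points, without excluding the fourth.

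Third, a reader might infer that control data are not collected at 4 months, or are deliberately discarded. Table 2 suggests that they are collected, and nothing forbids their use; the maintenance sentence simply does not use them.

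Fourth, a reader might infer that the bias rivals the whole confidence interval. The documents do not support that. They give no rate of change over 4 months, and the Background statement concerns child behaviour only, so it says nothing about drift in the FAD, DASS, PS or PSOC. An assumed drift of 3 T points is below the within-arm half-width at every correlation in the table (3.50 to 5.54).

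Finally, the controlled contrast has its own weakness: allocation alternates by date of injury, is not randomised, and yields 15 per arm. That is a reason to show the uncertainty, and it does not make the uncontrolled figure informative about maintenance.

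**Conclusion.** The point holds in this limited form. The maintenance analysis, as worded, cannot distinguish natural course from loss or persistence of effect, and it falls short of the comparison promised elsewhere in the same article. This is a choice that the text states, so it is more than a detail left to a fuller plan.

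The bias is *d*, point for point; its size is unknown, and on the Background's account its direction for child behaviour would be towards apparent loss of benefit. Reading *d* from the wait-list arm rests on two assumptions that the documents do not secure: that the arm is still untreated at time point 4, and that both arms drift alike despite non-randomised allocation. The weight is moderate: the wording should be corrected, but the feasibility aims and the end-of-programme comparison are untouched.

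**What to change.** Reconcile the maintenance sentence in Data analysis with Overall study design and Table 2.

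1. Report wait-list means and SDs at time point 4 beside those of the intervention group.
2. Report, with a 95% CI, either the between-group difference at time point 4 adjusted for the time-point-2 score (is an effect still present?) or the difference between arms in change from time point 3 to 4 (how much was lost?). Name the choice in advance.
3. Keep the within-arm means and SDs as description, and do not present them alone as evidence on maintenance.
4. State whether the wait-list group is still untreated at time point 4, and report how many of its families have started the programme by then.
5. Label the contrast preliminary, and say that it relies on similar drift in two non-randomised groups.

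**Cost.** If Table 2 is followed for both groups, no further data collection is needed; the change is to the analysis text, plus a count of programme starts in the wait-list group. The price is precision: the SE of the difference in change is √2 times that of the within-arm change (half-width 5.79 against 4.29 T points at an assumed *r* of 0.7), and any attrition widens both.

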### Study aims

The primary aim of the current study is to investigate the feasibility and acceptability of conducting Signposts with videoconferencing as the mode of clinician support. In particular, this study intends to investigate this in families where the child sustained the TBI in early childhood, an age group that may be particularly prone to post-TBI poor outcomes [35–37] but, to date, has been relatively neglected with minimal attention directed to development of age-appropriate evidence-based interventions targeting behaviour problems.

More specifically, the study objectives are to:Investigate the feasibility of delivering the programme with clinician support via videoconferencing, with the goal of developing a larger RCT. This will be investigated with the collection of data on sample retention rates, participant programme adherence, and duration to reach target sample size.Collect information to inform on the clinical practicality of delivery through this medium, including the duration of videoconference sessions, rate of technology difficulties that cause disruption to sessions, and the time frame for programme completion (in weeks).Explore the acceptability of the programme when delivered through this medium, with completion of a consumer satisfaction survey, as well as by enquiring on the participant’s comfort with using the technology. It is expected that, consistent with programme delivery through different modalities, the programme will have a high level of consumer satisfaction in this population when delivered with clinician support via videoconferencing.Explore preliminary clinical outcomes across those who completed the programme compared with those on a wait-list, in order to inform likely efficacy estimates for a fully powered RCT. Primary measures will assess child behaviour, while secondary outcome measures will assess parent distress, parenting disciplinary style, parenting sense of competency, and family functioning. These will be measured using questionnaires considered standard for research involving the Signposts programme (see, for example, Woods and colleagues [23]). It is expected that those who complete Signposts will report reductions in post-TBI child behaviour problems, parental distress, and dysfunctional parenting, while increasing family functioning and parental sense of competency.

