## Methods/design

### Overall study design

The current pilot study employs a two-arm, parallel non-randomised design, in which a treatment as usual wait-list group is compared with a group in which the ‘Signposts’ programme is completed with clinician support via videoconferencing (see Fig. 1). The wait-list group may access any therapies or treatments considered standard treatment for a paediatric TBI.

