#### Child behavioural outcomes

The pre-morbid, pre-intervention, and post-intervention behavioural functioning of the children is determined using the Child Behavior Checklist (CBCL) [42]. Two versions of the CBCL will be used. The preschool version of the CBCL is a standardised 100-item questionnaire, which was designed for use on children aged 1.5–5, while the school-aged version is a 113-item questionnaire designed for use on children aged 6–18. The age-appropriate version will be completed by the caregiver regarding their child’s behaviour. The current study used the three summary scores for analysis (total, internalising and externalising behaviour scales). *T* scores are derived for these scales (*M* = 50, SD = 10), where a *T* score greater than or equal to 60 denotes behaviour falling in the clinically significant range.

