### Sample size

The current feasibility study sample will aim to consist of 15 parents who will participate in the intervention and a further 15 allocated to the wait-list control group. Studies also exploring the feasibility of family-centred behaviour interventions in this population used similar sample sizes [49–52] and detected promising preliminary results. With recruitment in this population frequently difficult and slow, we aim to measure the duration of time taken to recruit this sample in order to guide estimates of recruitment duration for a larger RCT.

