## Discussion

This study is the first to investigate the feasibility and efficacy of a parenting training programme using videoconferencing as the support mode, for decreasing undesirable behaviours in children who sustained a TBI at an early age and improving parental post-TBI outcomes, such as mental health and sense of parenting efficacy. Preliminary findings of feasibility and efficacy of Signposts when delivered with an online support mode will pave the way for use of this method in a larger randomised controlled trial, with the aim of translation into clinical settings. For many families, when implemented clinically, online programme delivery would provide the opportunity to access services which would otherwise be costly and time consuming, particularly for those from more challenging socioeconomic backgrounds, or living in rural settings. This initial study also lays the foundation to further develop Signposts materials to be fully provided online.

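### Efficacy estimates for a fully powered RCT are a stated use of group means from 15 non-randomised families per arm, which are too imprecise for that, and no caution is given

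*Protocol article*

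**What the plan says.** The fourth objective in Study aims compares clinical outcomes between programme completers and the wait-list group, "in order to inform likely efficacy estimates for a fully powered RCT". Data analysis gives the method: post-intervention scores on the CBCL scales, FAD, DASS, PS and PSOC are compared across groups, and the authors "will report the mean and standard deviation of each group across these measures". After a sentence on change to 4 months within the intervention group, the section closes with "These findings may inform efficacy estimates for a larger RCT".

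Sample size sets the target at "15 parents who will participate in the intervention and a further 15 allocated to the wait-list control group". The reasons given are that comparable feasibility studies "used similar sample sizes [49–52] and detected promising preliminary results" and that recruitment in this population is slow. No precision target is given. Overall study design states: "The current pilot study employs a two-arm, parallel non-randomised design". The Discussion adds: "Preliminary findings of feasibility and efficacy of Signposts when delivered with an online support mode will pave the way" for a larger randomised trial.

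The primary aim is feasibility and acceptability. The outcome results are called preliminary throughout, but no sentence limits how precisely they can be read.

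**The concern.** A feasibility study may report outcome data by group. The difficulty is the purpose attached to them. An efficacy estimate for a powered trial has to be precise enough to separate a worthwhile effect from none, and 15 per arm does not give that. A point estimate from this study could be close to zero when the programme works well, or large when it does nothing. Anyone planning the next trial from this article is told that these findings may serve as efficacy estimates and is not warned how wide the uncertainty is. Because allocation is not randomised, the difference may also carry bias, which a confidence interval would not show.

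**Working it through.** The article states no power or precision calculation, so there is no figure to reproduce. The check asks how precise the planned comparison would be.

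**Inputs**
- n = 15 per arm (Sample size).
- SD = 10 for CBCL T scores, from "scores are derived for these scales (*M* = 50, SD = 10" (Child behavioural outcomes). This is the normative SD. The SD in this sample is unknown, so using 10 is an assumption.
- Unadjusted comparison of post-intervention scores, as Data analysis describes it.
- Two-sided 5% and 80% power for a later RCT. Both are assumptions; the article gives neither.

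**1. Interval for a mean difference**

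SE = SD × √(2/n) = 10 × √(2/15) = 3.65 T points.

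Half-width = t(0.975; 28 df) × SE = 2.048 × 3.65 = 7.5 T points, or 0.75 SD.

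The half-width is proportional to the SD. With 12 completers per arm (assumed), it rises to about 8.5 points.

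**2. Interval for a standardised difference d (noncentral t, 15 per arm)**

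| Observed d | 95% CI |
|---|---|
| 0.3 | -0.42 to 1.02 |
| 0.5 | -0.23 to 1.22 |
| 0.8 | 0.05 to 1.54 |

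Even an observed 0.8 is compatible with almost no effect.

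**3. What that would mean if the difference were used to size the RCT**

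This use is an inference, not something the article states. Per-arm sizes from the t distribution are:

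| Target d | n per arm |
|---|---|
| 1.2 | 12 |
| 0.8 | 26 |
| 0.5 | 64 |
| 0.3 | 176 |
| 0.2 | 394 |
| 0 or below | no finite size |

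The normal formula 2 × (1.96 + 0.84)² / d² gives 63 at d = 0.5, one fewer per arm. For an observed d of 0.5, the upper limit of 1.22 needs about 12 per arm, the point estimate 64, and the lower limit of -0.23 has no finite size.

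A simulation of 200,000 pilots with true d = 0.5, each RCT sized on the observed d by the normal formula, gave these results:
- In 63% of pilots the RCT size was wrong by more than a factor of 2, or the observed d was zero or negative. At true d = 0.3 and 0.8 this was 77% and 45%.
- Among pilots with a positive observed d, 55% led to an RCT with under 80% power and 31% to one with under 50%.

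**4. The SD as a planning input**

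With 28 df, the 95% limits for a pooled SD are the estimate multiplied by √(28/44.46) = 0.79 and √(28/15.31) = 1.35, so -21% to +35%. That is not tight, but it is bounded and usable. The SDs are already in the planned output.

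**The case against.** The wording is soft. The findings may inform efficacy estimates, which is compatible with weighing them alongside the earlier Signposts studies cited in the Background. The study quantities tied most directly to the RCT are feasibility ones: retention, adherence and time to reach the target sample. Any reader with means, SDs and n can work out the interval for the post-intervention difference, and a journal article may leave intervals and pre-post correlations to a fuller document. Adjusting for the pre-intervention score could also narrow the interval.

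Much of this stands, and it rules out three stronger readings that a reader might infer.
- *The RCT will be sized on the pilot effect.* No sentence says so. No target difference or power rule for the RCT appears, so step 3 above is conditional.
- *The RCT will proceed only if efficacy looks good.* There is no such rule, so selection of an overestimate cannot be charged to the plan. The Discussion sentence also covers feasibility and concerns taking the delivery method into a larger trial.
- *The plan fails to carry the SD forward.* It does report the SD by group, among the findings said to inform the RCT.

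The absence of an interval or a pre-post correlation would not be a finding by itself. What the objection does not remove is the stated purpose. Both the objective and the analysis section name efficacy estimates for the RCT as a use of these data, and a fuller document that added intervals would leave that purpose in place.

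**Conclusion.** The point holds as a mismatch between a stated use and what the design can deliver. An unadjusted difference from 15 per arm carries a 95% interval of about ±0.75 SD, and an observed d of 0.5 is compatible with anything from a small adverse effect to a very large benefit. The conversion to 7.5 T points assumes the normative SD of 10. The RCT sizes assume 80% power and two-sided 5% and apply only if the difference were used for sizing. Non-randomised allocation adds possible bias on top of the sampling error. The feasibility and acceptability aims are unaffected. The change is worth making because it costs little and alters what readers may conclude from the outcome data.

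**What to change.** 1. Report each between-group post-intervention difference with a 95% confidence interval, next to the group means and SDs.
2. Reword the fourth objective and the last line of Data analysis. Suggested text: *Between-group differences will be reported with 95% confidence intervals. They are expected to be imprecise, may be biased by non-randomised allocation, and will not serve as the target difference of a later RCT. The study's planning inputs for that trial are the outcome SDs, with their uncertainty, retention and recruitment time.*
3. Qualify the efficacy wording in the Discussion to match.

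The cost is a few extra statistics per outcome and a more modest claim. Design, sample size and data collection stay as they are.
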